## Abstract

**Background:**

Neonatal hypoglycaemia is common, affecting up to 15 % of newborn babies and 50 % of those with risk factors (preterm, infant of a diabetic, high or low birthweight). Hypoglycaemia can cause brain damage and death, and babies born at risk have an increased risk of developmental delay in later life.

Treatment of hypoglycaemia usually involves additional feeding, often with infant formula, and admission to Neonatal Intensive Care for intravenous dextrose. This can be costly and inhibit the establishment of breast feeding.

Prevention of neonatal hypoglycaemia would be desirable, but there are currently no strategies, beyond early feeding, for prevention of neonatal hypoglycaemia. Buccal dextrose gel is safe and effective in *treatment* of hypoglycaemia. The aim of this trial is to determine whether 40 % dextrose gel given to babies at risk prevents neonatal hypoglycaemia and hence reduces admission to Neonatal Intensive Care.

**Methods/design:**

Design: Randomised, multicentre, placebo controlled trial.

Inclusion criteria: Babies at risk of hypoglycaemia (preterm, infant of a diabetic, small or large), less than 1 h old, with no apparent indication for Neonatal Intensive Care Unit admission and mother intends to breastfeed.

Trial entry & randomisation: Eligible babies of consenting parents will be allocated by online randomisation to the dextrose gel group or placebo group, using a study number and corresponding trial intervention pack.

Study groups: Babies will receive a single dose of 0.5 ml/kg study gel at 1 h after birth; either 40 % dextrose gel (200 mg/kg) or 2 % hydroxymethylcellulose placebo. Gel will be massaged into the buccal mucosal and followed by a breast feed.

Primary study outcome: Admission to Neonatal Intensive Care.

Sample size: 2,129 babies are required to detect a decrease in admission to Neonatal Intensive Care from 10–6 % (two-sided alpha 0.05, 90 % power, 5 % drop-out rate).

**Discussion:**

This study will investigate whether admission to Neonatal Intensive Care can be prevented by prophylactic oral dextrose gel; a simple, cheap and painless intervention that requires no special expertise or equipment and hence is applicable in almost any birth setting.

**Trial registration:**

Australian New Zealand Clinical Trials Registry - ACTRN 12614001263684.

## Background

### Significance of the project

Neonatal hypoglycaemia is common in the first few days after birth. Up to 15 % of normal newborn babies will have low blood glucose concentrations [1]. However, the incidence in babies who have risk factors is much greater: up to 50 % in infants of diabetic mothers, [2] large and small babies [3] and 66 % in preterm babies [4].

Glucose is the primary energy source for the brain, and neonatal hypoglycaemia is associated with brain damage and death [4–6]. Babies born at risk for neonatal hypoglycaemia have an increased risk of developmental delay in later life [7–10]. Indeed, it has been reported that neonatal hypoglycaemia is the only neonatal morbidity independently associated with later developmental delay in late preterm babies [11]. While it is uncertain what degree or duration of hypoglycaemia is necessary before morbidity occurs, it is known that even babies without symptoms can have adverse outcomes [4, 6]. Thus hypoglycaemia is common and the only readily preventable cause of brain damage in the newborn.

### Standard management

Blood glucose concentrations normally fall in the first 1–2 h after birth, and then begin to rise again as babies mobilise their body stores of fat and glycogen and begin to feed. In some babies, this physiological fall in blood glucose concentration may persist and, if untreated, potentially may cause permanent brain damage. Since hypoglycaemia is often asymptomatic, the recommended approach is to monitor blood glucose concentrations in all babies at risk, usually by repeated heel-prick blood samples, commonly 4 hourly, in the first 1–2 days [12, 13]. This is painful for the baby and distressing for all concerned.

It is generally accepted that blood glucose concentrations < 2.6 mmol/L require treatment [4, 14, 15]. Standard management of babies in whom low glucose concentrations are detected is to minimise the duration of hypoglycaemia and ensure the glucose is ‘normalised’ as quickly as possible [6, 16]. This commonly requires admission to Neonatal Intensive Care Unit (NICU) for intravenous glucose, separating mother and baby and delaying the establishment of breast feeding as well as incurring high healthcare costs.

The American Academy of Pediatrics advises early identification of the at-risk baby and institution of prophylactic measures to prevent neonatal hypoglycaemia [12]. This is commonly achieved by early feeding, often with supplemental formula milk [12, 17]. However, supplementing with formula milk has been shown to reduce longer term breastfeeding rates [18]. Furthermore, there are both human and experimental data indicating that supplementation of newborns in the first two weeks may have long-term effects on metabolic outcomes. Even brief periods of nutritional supplementation in preterm babies result in altered control of blood pressure and insulin regulation in adolescence [19, 20]. Thus, interventions that prevent hypoglycaemia without supplemental, artificial feeds may help maintain breastfeeding and also have benefits for both neurodevelopmental and metabolic outcomes.

### Recent advances

#### Oral dextrose gel

Harris et al. demonstrated that treatment of neonatal hypoglycaemia with oral dextrose gel was more effective than feeding alone in reversing the hypoglycaemia, and also reduced the rate of NICU admission for this problem and reduced the rate of formula feeding at two weeks of age [21]. Importantly, the gel was well-tolerated, cheap, simple and safe to administer, and was acceptable to families and caregivers.

### Aim

We therefore propose a randomised controlled trial to determine if prophylactic oral dextrose gel given to newborns at risk prevents neonatal hypoglycaemia and thus reduces NICU admission, improves breast feeding rates and reduces costs as well as potentially reducing the risk of later adverse outcomes.

### Hypothesis

The primary hypothesis of this study is that, compared to placebo and standard care, prophylactic 40 % oral dextrose gel given to babies at risk of hypoglycaemia (infant of diabetic mother, preterm, large or small for dates, or other) reduces admission to the Neonatal Intensive Care Unit.

## Methods/design

### Ethics

Ethics approval has been obtained from the Health and Disability Ethics Committees of New Zealand (ethics reference 13/NTA/8) and by the local institutional research review committees for each centre. The ethics committee is notified of any amendments to the study protocol.

### Study design

A multicentre, randomised, placebo controlled trial comparing 40 % dextrose gel with placebo to prevent hypoglycaemia in the first 48 h in babies born at risk.

## Study population

### Inclusion criteria

Babies born at risk of hypoglycaemia, defined as satisfying at least ONE of the following:Infants of diabetic mothers (any type of diabetes)Preterm (< 37 weeks’ gestation)Small (< 2.5 kg or < 10th centile on population or customised birthweight chart)Large (> 4.5 kg or > 90th centile on population or customised birthweight chart)

AND satisfy ALL of the following:≥ 35 weeks’ gestationBirth-weight ≥ 2.2 kg< 1 h oldNo apparent indication for NICU admission at time of randomisationUnlikely to require admission to NICU for any other reasons e.g. respiratory distressMother intending to breast-feed

### Exclusion criteria

Major congenital abnormalityPrevious formula feed or intravenous fluidsPrevious diagnosis of hypoglycaemiaAdmitted to NICUImminent admission to NICU.

### Primary outcome

#### Admission to NICU

This is defined as admission to NICU (or Special Care Baby Unit (SCBU) for the hospitals which use that name) for > 4 h [22].

### Secondary outcomes

Hypoglycaemia (any blood glucose concentration < 2.6 mmol/L in the first 48 h);Admission to NICU for hypoglycaemia;Hyperglycaemia (any blood glucose concentration > 10 mmol/L);Breastfeeding at discharge from hospital (full or exclusive);Received any formula prior to discharge from hospital;Formula feeding at 6 weeks of age;Cost of care until primary discharge home;Maternal satisfaction (via telephone questionnaire at 6 weeks);Neurosensory disability at 2 years’ corrected age (any of: legal blindness; sensorineural deafness requiring hearing aids; cerebral palsy; Bayley Scale of Infant Development Version III cognitive, language or motor score lower than one standard deviation below the mean).

## Trial entry

### Informed consent

Parents of babies who are likely to become eligible (maternal diabetes, likely late preterm birth, or anticipated high or low birth weight) will be identified through lead maternity carers and antenatal clinics and provided with an information sheet as early as is feasible. Written informed consent will normally be obtained before the birth.

## Randomisation

Eligible babies for whom consent has been obtained will be enrolled and randomised immediately after birth. Babies will be assigned randomly via an internet randomisation service to the dextrose or placebo group with priority stratification for collaborating centre and risk factor (i.e. maternal diabetes, preterm, small or large).

### Discontinuation of randomised treatment

The allocated treatment can be stopped at any time at the request of the parents, or by the neonatologist caring for the baby if (s) he feels that stopping the treatment would be in the best interest of the baby. The baby will still be followed up and analysed according to the intention-to-treat principle.

## Study groups

The study intervention drug (both dextrose gel and placebo) will be supplied by Biomed Ltd (Auckland, New Zealand) in identically labelled, pre-filled syringes of either 40 % dextrose gel or identical appearing 2 % hydroxymethylcellulose placebo gel in individually pre-labelled trial packs. Each participating centre will have a supply of study packs held in a medications fridge. The staff member randomising the baby will receive a study number corresponding to a pre-labelled study pack, and also the volume of gel (0.5 ml/kg) to be administered. The inside of the baby’s cheek will be dried with a gauze swab, and the study gel massaged into the buccal mucosa at one hour after birth.

In order to determine the most effective dose in prevention of neonatal hypoglycaemia, we undertook a dosage trial (registered with the Australian New Zealand Clinical Trials Registry ACTRN12613000322730). The dose selected of 0.5 ml/kg (200 mg/kg) 40 % dextrose gel at 1 h of age had maximal efficacy in prevention of hypoglycaemia, with the fewest limitations (i.e. was easy to administer, well tolerated and with minimal additional workload or financial cost).

### Blood glucose analysis

The initial blood glucose concentration will be measured at 2 h, as is common practice. Subsequent management will be according to hospital standard practices. All blood glucose concentrations will be analysed by the gold standard glucose oxidase method, either with a portable blood glucose analyser (e.g. iSTAT, Abbott Laboratories, Abbott Park, IL USA) or a combined metabolite/blood gas analyser (e.g. ABL 700, Radiometer Ltd, Copenhagen, Denmark).

## Follow up after birth until time of discharge from hospital

### Surveillance

Babies will be monitored according to routine clinical practice. This includes pre-feed blood glucose measurements 2–4 hourly for at least the first 12 h, and until there have been 3 consecutive measurements > 2.6 mmol/L. If the baby becomes hypoglycaemic (blood glucose concentration < 2.6 mmol/L) then the hospital protocol will be followed for management of hypoglycaemia, including the administration of treatment dextrose gel and supplementary feeds if relevant. We will monitor for serious adverse events (seizures and death) and other adverse events; hyperglycaemia (as above), late hypoglycaemia (blood glucose concentration < 2.6 mmol/L for the first time after 12 h of age), delayed feeding (failure to establish breastfeeding without supplements by the end of day 3) and systemic sepsis [22].

## Follow-up after primary hospitalisation

Parent (s) of participants will be contacted on day 3 (if already discharged home) and 6 weeks after birth to complete a telephone questionnaire. This will include details of the current feeding regime, and at 6 weeks, parental satisfaction with participation in the trial and health status of the baby. We will maintain contact with babies and their families. At 2 years’ corrected age all families will be contacted to arrange a developmental assessment to investigate longer-term outcomes. We will provide results when available to those who have informed us that they wish to be made aware of the outcome of the trial.

## Data analysis

The primary outcome of NICU admission will be analysed by logistic regression, stratifying by collaborating centre. Secondary analyses will adjust for potentially confounding variables: reason for risk of hypoglycaemia (infant of diabetic, late preterm, small or large), sex, gestational age, and mode of birth (vaginal vs caesarean section). Continuous data will be compared by Student’s *t* test, or the Mann–Whitney *U* test if the data are not normally distributed and cannot be converted to near-normality by simple transformation. Data with repeated points, such as blood glucose concentrations, will be compared using mixed model techniques, modelling the main effect of treatment group allocation, time and their interaction, with significant main effects and interactions tested using the method of Tukey. All tests will be two-tailed, with P < 0.05 considered significant. The data will be analysed on an intention-to-treat basis, and any baby who dies or for whom the primary outcome of NICU admission cannot be determined will be assigned the worst case outcome of NICU admission.

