### Power and sample size

Based on data from Auckland City Hospital and Waikato Hospital, 10 % of at-risk babies will require admission to NICU. A trial of 2,129 babies (1,014 in each arm, with continuity correction and allowing for 5 % drop-out rate), will have 90 % power to detect a 40 % relative reduction (absolute reduction of 4 %) in admission to NICU from 10–6 % with two-sided alpha of 0.05.

Should this study show that dextrose gel is effective at preventing NICU admission, it will be critical to find out if this also improves long-term outcomes for babies. A sample size of 2,014 babies would allow us to detect a reduction in the number of children with one or more low developmental scores (<1SD below the mean) on a Bayley Infant Scales of Development Edition III assessment at 2 years from 40–33 %.

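### Randomisation is stratified by centre and risk factor, but the primary logistic model accounts for centre only, so the primary test may be slightly conservative

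*Protocol article*

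**What the plan says.** The Randomisation section assigns babies by an internet service, with "priority stratification for collaborating centre and risk factor", and lists the risk factors as maternal diabetes, preterm, small and large.

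The Data analysis section fixes the primary model: "The primary outcome of NICU admission will be analysed by logistic regression, stratifying by collaborating centre". The next sentence places risk factor elsewhere: "Secondary analyses will adjust for potentially confounding variables: reason for risk of hypoglycaemia", in a list that also holds sex, gestational age and mode of birth.

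The Power and sample size section assumes that "10 % of at-risk babies will require admission to NICU" and plans for a fall to 6%, with 90% power and a two-sided alpha of 0.05.

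**The concern.** The primary analysis uses one of the two stratification factors and omits the other without giving a reason. The article names the primary model and assigns risk factor to the secondary analyses, so this is a stated choice. It is not a detail left to the analysis plan.

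Stratifying on a variable that predicts the outcome balances it between arms, and this reduces the chance variation in the treatment comparison. A model that leaves the variable out does not know about that balance. Its standard error is then larger than the true sampling variability, the test rejects less often than 5% under the null, and a little power is lost.

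The label of potential confounder also does not fit. Stratified randomisation already balances risk factor between arms. The reasons to adjust for it are to match the analysis to the design and to use a prognostic variable.

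Risk factor is plausibly prognostic. The Background section reports hypoglycaemia in up to 50% of infants of diabetic mothers and of large and small babies, against 66% of preterm babies, and it says that low glucose commonly leads to NICU admission.

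**Working it through.** **1. The plan's own sample size.** Inputs from Power and sample size: p1 = 0.10, p2 = 0.06, two-sided alpha 0.05, power 90%, continuity correction, 5% drop-out. With a mean rate of 0.08 and d = 0.04:

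- n = [1.96·√(2·0.08·0.92) + 1.2816·√(0.10·0.90 + 0.06·0.94)]² / 0.04² = 964.6, so 965 per arm without the correction.
- With the correction: (n/4)·[1 + √(1 + 4/(n·d))]² = 1,014 per arm, or 2,028 in total.
- 2,028 × 1.05 = 2,129.4, which matches the stated 2,129.

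The sample size reproduces and does not depend on the point raised here.

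**2. Why the test becomes conservative.** Let w be the share and p the control admission rate of each risk group, with overall rate 0.10. The share of outcome variance that lies between groups is R² = Σ w(p − 0.10)² / (0.10·0.90). With balance within groups, the true standard deviation under the null is about √(1 − R²) times the standard error from the model without risk factor. The actual type I error is therefore about 2·[1 − Φ(1.96/√(1 − R²))].

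The article gives neither w nor p. The values below are assumed, in the order diabetes / preterm / small / large.

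| Scenario | Shares (%) | Control rates (%) | R² | Type I error by formula |
|---|---|---|---|---|
| Equal | 40/10/30/20 | 10/10/10/10 | 0 | 0.050 |
| Mild | 73/5/12/10 | 10/15/10/7.5 | 0.002 | 0.050 |
| Moderate | 40/10/30/20 | 10/20/8/8 | 0.013 | 0.048 |
| Strong | 40/10/30/20 | 7/30/8/9 | 0.050 | 0.044 |
| Extreme | 40/20/20/20 | 4/34/4/4 | 0.160 | 0.032 |

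For the strong scenario: 0.4·0.03² + 0.1·0.20² + 0.3·0.02² + 0.2·0.01² = 0.0045, and 0.0045/0.09 = 0.05. Then 1.96/√0.95 = 2.011, which gives 0.044.

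**3. Simulation.** 10,000 trials per scenario, 1,014 babies per arm, allocation balanced within risk groups, overall rates held at 10% and 6% (10% in both arms for the null), logistic Wald test. Centre effects were not simulated.

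| Scenario | Type I error, without → with risk factor | Power, without → with | Gain (points) |
|---|---|---|---|
| Equal | 0.051 → 0.052 | 91.5% → 91.6% | 0.1 |
| Mild | 0.053 → 0.054 | 91.6% → 91.6% | 0.05 |
| Moderate | 0.047 → 0.049 | 91.1% → 91.3% | 0.3 |
| Strong | 0.043 → 0.049 | 91.9% → 92.5% | 0.6 |
| Extreme | 0.033 → 0.051 | 93.1% → 94.8% | 1.7 |

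Gains are taken from the unrounded powers. The Monte Carlo standard error of a type I error near 0.05 is √(0.05·0.95/10,000) = 0.002, so the equal and mild rows do not differ from 0.05. The other three agree with the formula.

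**4. Where the gain comes from.** At the planned effect, the standard error from the model without risk factor is 0.1696 against a true variability of 0.1667 (strong), and 0.1694 against 0.1581 (extreme). Adding risk factor raises the model standard error, to 0.1735 and 0.1818. It also moves the mean log odds ratio further from zero: from −0.558 to −0.584 (strong; odds ratio 0.573 to 0.558) and from −0.557 to −0.642 (extreme; 0.573 to 0.526). The second change outweighs the first, so power rises.

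**The case against.** The case for leaving the plan alone is that the effect is small, conservative and dependent on assumed rates. Entry is limited to babies of at least 35 weeks and 2.2 kg with no apparent indication for NICU admission, which gives reason to expect a narrower spread than the strong or extreme scenarios. A risk-adjusted analysis is already planned, so risk factor is not lost. Adjustment also changes what the odds ratio describes. All of this stands and limits the point to a minor one, but none of it explains why only one stratification factor is in the primary model.

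A reader might infer more than the document supports:

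- *That the primary analysis is invalid or the trial underpowered.* The error is on the safe side, and with overall rates of 10% and 6% the simulated power without risk factor is at least 91.1% in every scenario. A lower figure can arise if an odds ratio of 0.574 is applied within each risk group. With assumed shares of 50/15/20/15% and rates of 6/30/9/5%, the overall rates become 10.05% v 6.24%. A simulation of 2,022 babies in 6 centres on that basis gave 88.8% power, but that is a smaller effect than the one planned.
- *That the omission costs precision.* For a log odds ratio this is the wrong description, because adjustment raises the standard error. What is lost is power.
- *That two analyses would compete near P = 0.05.* The Data analysis section already ranks them: the centre-stratified model is primary and the adjusted models are secondary.

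**Conclusion.** The mismatch between the Randomisation and Data analysis sections is plain on the text. Its consequence is small: a somewhat conservative primary test, with type I error of about 0.047 under moderate and 0.043 under strong assumed differences, and a power loss of about 0 to 0.6 points, reaching about 1.7 points only if the groups differ to an extreme degree. If the groups do not differ in admission risk, nothing is lost. These sizes rest on assumed group shares and admission rates and on a simulation without centre effects. The direction follows from the design whenever risk factor is prognostic. Severity is minor.

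**What to change.** State that the primary outcome will be analysed by logistic regression adjusted for both randomisation stratification factors, centre and risk-factor category as entered at randomisation. Keep sex, gestational age and mode of birth for the secondary adjusted analysis, and stop describing risk factor as a potential confounder. Note in the text that the reported odds ratio is then conditional on risk factor as well as centre. If the centre-only model is preferred, give the reason.

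The cost is one clause and three extra model parameters (four risk categories). The category is recorded at randomisation, so no new data and no additional babies are needed.

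### The primary model for NICU admission adjusts for centre only, leaving out the risk-factor randomisation stratum and other baseline covariates, and names no effect on the risk scale used for sizing

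*Protocol article*

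**What the plan says.** The Data analysis section fixes the primary method: "The primary outcome of NICU admission will be analysed by logistic regression", with stratification by collaborating centre. It continues: "Secondary analyses will adjust for potentially confounding variables", and lists reason for risk of hypoglycaemia, sex, gestational age and mode of birth. It names no effect measure for NICU admission.

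The Randomisation section places allocation immediately after birth and stratifies it by two factors, collaborating centre and risk factor (maternal diabetes, preterm, small or large).

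The Power and sample size section states the target on the risk scale: a "40 % relative reduction (absolute reduction of 4 %) in admission to NICU from 10–6 % with two-sided alpha of 0.05". The planned size is "2,129 babies (1,014 in each arm, with continuity correction and allowing for 5 % drop-out rate".

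**The concern.** Three features of the text do not fit together well.

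1. **A randomisation stratum is missing from the deciding model.** Allocation is stratified by centre and risk factor, but the primary model takes account of centre only. Risk factor appears only in the secondary analyses. Leaving out a prognostic stratification factor does not bias the test towards false positives, but it gives up precision that the stratified design was set up to deliver.
2. **The covariates carry the wrong label.** Reason for risk, sex, gestational age and mode of birth are all settled before a baby is randomised. Any imbalance between arms is chance, and for risk factor the stratification limits even that. Calling them potentially confounding invites a reader to take a change between the primary and adjusted odds ratios as bias removed. An odds ratio moves away from 1 when prognostic covariates are added, even under perfect balance (non-collapsibility).
3. **The scale differs from the sizing.** A logistic coefficient is a log odds ratio, whereas the trial is sized on a relative risk of 0.60 and a risk difference of 4 points.

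At stake are a modest amount of precision and the clarity of the headline result. The validity of the test is not in question.

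**Working it through.** **Inputs from the Power and sample size section:** placebo risk 10%, dextrose risk 6%, two-sided alpha 0.05, power 90%, 1,014 per arm, 2,129 in total, continuity correction, 5% drop-out. **Assumed, not in the article:** the strength of the covariates, expressed as the SD of their combined linear predictor on the log-odds scale, taken over 0.25 to 1.5.

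**1. The plan's own figure.** With mean risk 0.08 and difference 0.04:

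n = [1.960 × √(2 × 0.08 × 0.92) + 1.282 × √(0.10 × 0.90 + 0.06 × 0.94)]² / 0.04² = 964.6, so 965 per arm.

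Continuity correction: (964.6 / 4) × [1 + √(1 + 4 / (964.6 × 0.04))]² = 1,013.99, so 1,014 per arm, as stated.

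Total: 2 × 1,014 × 1.05 = 2,129.4, which matches 2,129. (Dividing by 0.95 instead gives 2,135, a trivial difference.)

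**2. The scale gap.**
- Relative risk = 0.06 / 0.10 = 0.600
- Odds ratio = (0.06 / 0.94) / (0.10 / 0.90) = 0.574

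Read as a percentage reduction, that is 43% in odds against 40% in risk.

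**3. Power of the planned test.** SE of the log odds ratio = √[1 / (1,014 × 0.10 × 0.90) + 1 / (1,014 × 0.06 × 0.94)] = 0.169. The effect is |ln 0.574| = 0.554, and 0.554 / 0.169 = 3.29. Power = Φ(3.29 − 1.96) = 90.8%. The expected 95% CI around 0.574 runs from about 0.41 to 0.80. The planned size therefore serves the logistic test as well as the comparison of proportions (91.4% without continuity correction).

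**4. What adjustment does to the odds ratio and to precision.** The marginal risks are held at 10% and 6%, the arms are perfectly balanced, and the covariate linear predictor is normal with the assumed SD. The conditional odds ratio is solved numerically. Explained variance is Var(p(x)) / (0.08 × 0.92) at an overall risk of 8%.

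| Assumed SD | Conditional OR | Shift from 0.574 | Outcome variance explained |
|---|---|---|---|
| 0.25 | 0.573 | 0.3% | 0.5% |
| 0.5 | 0.568 | 1.1% | 1.9% |
| 0.8 | 0.558 | 2.9% | 5.1% |
| 1.0 | 0.548 | 4.6% | 8.0% |
| 1.5 | 0.513 | 10.6% | 17.1% |

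In every row the standardised relative risk stays at 0.600 and the risk difference at 4.0 points, because the marginal risks have not changed. The last column is roughly the proportional fall in the variance of the risk difference when the covariates are used. At 5.1%, the standard error falls by 1 − √(1 − 0.051) = 2.6%; at 8.0%, by 1 − √(1 − 0.080) = 4.1%.

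**The case against.** The strongest reply is that the article fixes a model and not a summary measure. A logistic model can yield a standardised relative risk and risk difference, and a journal article may leave the choice of measure to an analysis plan that is not shown. Sizing on two proportions and testing by logistic regression is routine, since the null hypothesis is the same on every scale. A centre-adjusted primary analysis with covariate adjustment as secondary is also a legitimate prespecified choice.

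Much of this stands, and it rules out stronger readings that a reader might be tempted to make:

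- **That the trial will be reported only as odds ratios.** The article does not say so; no effect measure is named for NICU admission.
- **That the primary and adjusted odds ratios cannot be compared.** For an assumed SD up to 1.0 the shift is under 5%, small beside an expected interval of about 0.41 to 0.80.
- **That the sample size or power is wrong.** Both reproduce.
- **That the odds ratio seriously exaggerates the effect.** At these risks the gap is 0.574 against 0.600. It would be wider for a common outcome such as hypoglycaemia, but the article names no model for binary secondary outcomes.

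What the reply does not answer is the part that the article does fix: which variables enter the deciding model, and what the others are called. The Randomisation section makes risk factor a stratum, the Data analysis section leaves it out of the primary model, and the same section describes it as a potential confounder. An unseen plan could add an effect measure without touching any of that.

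**Conclusion.** The point holds in a limited form. The primary model should reflect both randomisation strata and can use the other named baseline covariates, and the result is best stated on the scale on which the trial was sized. The gain is modest: about 2% to 8% of outcome variance for an assumed covariate SD of 0.5 to 1.0, or roughly a 1% to 4% smaller standard error. That range rests on covariate strengths that the article does not give, and on the strength being additional to whatever centre already explains. The planned analysis is valid as it stands: type I error is not inflated, 1,014 per arm and 2,129 in total are correct, and power is about 91%. The case for change is that the improvement is nearly free and removes a misleading label.

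**What to change.** In the Data analysis section (and in the analysis plan, if it follows the article):

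1. Include centre and reason for risk, the two randomisation strata, in the primary logistic model, together with sex, gestational age and mode of birth.
2. Report the standardised relative risk and risk difference for NICU admission, each with a 95% CI, as the primary result.
3. Show the centre-only analysis on the same scale as a sensitivity result.
4. Describe the covariates as prognostic instead of potentially confounding.

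The change should be made before unblinding. It needs no new data and no change to sample size or conduct. The cost is a few sentences and one post-estimation step, with the CI from the delta method or bootstrap, plus slightly more modelling in the primary analysis.
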